The aim of this study is to understand the disease and prescribing trends related to AF in general practice. We also aim to develop a system to monitor practice-level indicators for AF of the same trends and evaluate the usability of this system. The primary objective of this study is to investigate if people with newly diagnosed AF treated with DOACs versus warfarin have any difference in stroke or all-cause mortality in long-term follow-up. The secondary objectives of this study are to develop an AF dashboard as an intervention method at a practice level and to evaluate the usability of the AF dashboard.

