## Methods

### Study Design

This study combines qualitative and quantitative methods and therefore, was planned as a mixed method study [9-11]. It was run within the Oxford Royal College of General Practitioners Research and Surveillance Centre (RCGP RSC) sentinel network of general practices. The mixed method study was conducted in 2 phases. Phase 1 was a quantitative analysis of AF data. We conducted a repeated cross-sectional study to identify those patients diagnosed with AF during 2009-2019 and identified current therapeutic management of their AF. Phase 2 involved development and evaluation of a dashboard for monitoring data quality for AF. The dashboard provides the general practices in the RCGP RSC sentinel network an access to quality indicators related to AF management that are updated weekly.

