#### Case Ascertainment

We used Read codes and CTV3 codes used in primary care CMR systems to identify patients with AF. Pay-for-performance (P4P) for chronic disease management has improved data quality related to AF in the recent past [15]. We excluded patients who had a previous stroke and those not on British National Formulary–recommended dose of DOAC. We included patients over 18 years with code for the diagnosis of AF who had been registered at any point between 2008 and 2019.

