#### Exposures and Outcomes

We considered the exposure as continuous anticoagulant prescription for the first time after receiving an AF diagnosis. Although almost all anticoagulant prescriptions in the United Kingdom are issued from primary care if an anticoagulant is started in a hospital, we measured exposure from the first general practice prescription. We excluded patients who had an interval of greater than 90 days between anticoagulant prescriptions.

Outcomes are first records of stroke and all-cause mortality based on previously published Read codes [16,17] Stroke was included regardless of etiology, an approach used in other studies [18,19]. Study participants were followed for stroke and all-cause mortality till the end of the study period.

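### The open registration rule leaves previous stroke, new AF, first anticoagulant use and baseline comorbidity not reliably ascertained in patients who joined a practice shortly before entry

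*Protocol article*

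**What the plan says.** The inclusion rule under Case Ascertainment covers adults with an AF code "who had been registered at any point between 2008 and 2019". The same section states: "We excluded patients who had a previous stroke and those not on British National Formulary–recommended dose of DOAC". It gives no look-back period for either rule.

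The primary objective at the end of the Introduction asks whether "people with newly diagnosed AF treated with DOACs versus warfarin have any difference in stroke or all-cause mortality". Under Exposures and Outcomes, exposure is a patient's first continuous anticoagulant prescribing after the AF diagnosis, counted from the first prescription issued in general practice. On endpoints, that section says: "Outcomes are first records of stroke and all-cause mortality".

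Under Covariates, the analysis adjusts for several components of the stroke risk score as they stood at baseline. Under Statistical Analysis, AF incidence and prevalence are to be estimated for each year.

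Study Design says the study was to "identify those patients diagnosed with AF during 2009-2019". No section requires a patient to have been registered for any length of time before diagnosis or before the index prescription.

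**The concern.** Four elements of the plan depend on what was recorded before the index date: absence of a previous stroke, newness of the AF, first use of an anticoagulant, and the baseline comorbidities. The data are coded records from participating practices. If a patient joined a practice days before the first prescription there, the absence of a code is weak evidence that the condition was absent.

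The outcome definition adds to this. The stroke endpoint is a first record. The same gap that lets a patient with an old stroke pass the exclusion can therefore turn that stroke into an outcome if it is coded later. Likewise, an old AF diagnosis entered at joining can enter the yearly incidence as a new case.

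At stake are the stroke part of the primary comparison, the adjustment for confounding, and the AF incidence estimates.

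**Working it through.** **Reading the sections together.** The registration window opens in 2008 and the diagnosis window in 2009. This is a gap in calendar time, not a look-back for each patient: someone who joined in 2018 and was prescribed an anticoagulant within days meets the rule. The Discussion mentions missing or incomplete data in general terms. Its remedy, an ontological approach that considers variation between practices, does not deal with time since registration.

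**No figure to reproduce.** The article gives no event rate, sample size or power for phase 1. The arithmetic below only illustrates possible size, and every input is an assumption.

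**Illustration 1: effect on the stroke risk ratio.** Assume a warfarin-arm stroke risk of 4% and a true ratio of 0.80, so the DOAC risk is 0.04 × 0.80 = 0.032. Let j be the share of recent joiners and s the share of them with an uncoded old stroke. Assume half of those strokes are first coded after the index date.

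- False-event risk: f = j × s × 0.5
- False share of warfarin-arm strokes: f / (0.04 + f)
- Ratio with equal errors: (0.032 + f) / (0.04 + f)
- Ratio with unequal errors: 1.5f in one arm and 0.5f in the other

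| j | s | f | False share | Equal errors | More in DOAC arm | More in warfarin arm |
|---|---|---|---|---|---|---|
| 3% | 5% | 0.00075 | 1.8% | 0.804 | 0.820 | 0.787 |
| 8% | 12% | 0.0048 | 10.7% | 0.821 | 0.925 | 0.729 |
| 15% | 12% | 0.0090 | 18.4% | 0.837 | 1.022 | 0.682 |

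For the last row: equal errors give 0.041 / 0.049 = 0.837; more in the DOAC arm gives 0.0455 / 0.0445 = 1.022; more in the warfarin arm gives 0.0365 / 0.0535 = 0.682.

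**Illustration 2: false share under other assumptions.** Take genuine strokes as 4.5% (1.5% per year for 3 years). Let r be the share of recent joiners, s the share of them with a previous stroke, and q the share of those strokes entered after the index date under a new date. The false share is rsq / (rsq + 0.045).

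- 5%, 10%, 20%: 0.001 / 0.046 = 2.2%
- 10%, 15%, 30%: 0.0045 / 0.0495 = 9.1%
- 15%, 20%, 50%: 0.015 / 0.060 = 25%

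The last line multiplies three high values and is an upper scenario.

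**Equality between arms.** The document gives no reason to assume it. The Introduction notes that warfarin was in use for many years before DOACs, so a long-standing warfarin user who changes practice could look like a new starter. How often this happens is not known.

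**The case against.** The strongest reply is that a journal article condenses a fuller protocol, and that look-back windows, event dating and the handling of history-of codes usually sit in that fuller document or in the cited code lists. The inclusion sentence also has to serve the yearly prevalence counts, for which an open registration frame is natural. This stands in part. Event dating and code selection may well be settled in material not shown. The registration rule is different: the article states it, and states it as open. A prior-registration requirement would narrow that sentence rather than add detail to it.

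A reader might infer that the history of recent joiners is unknown. The document does not say that earlier records are unavailable after joining, so the supportable wording is that history is not reliably ascertained. A reader might also infer that late-entered strokes do count as outcomes. The definition permits it, but nothing shows that it happens or how often. The chain is narrow: the practice must have coded AF and prescribed an anticoagulant, left an old stroke uncoded, and later coded it in a way that counts as an outcome.

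It can further be objected that 12 months of registration does not prevent an old stroke from being coded later still. That is partly right. History entered during those 12 months falls before the index date and triggers the exclusion, but later entries need a rule on event dates and code types as well.

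Finally, phase 1 extraction and analysis were finished in 2019, so the change is more than one line of text. It is nevertheless a filter on retrospective data.

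**Conclusion.** The concern holds as a weakness in a stated rule. For recent joiners, four elements that need earlier history are not reliably ascertained, and the first-record definitions allow old strokes and old AF to be counted as new.

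Size and direction cannot be fixed from the document. It is tempting to conclude that the stroke comparison is diluted toward no difference. That follows only if errors are equal between arms, and the effect is then mild (0.80 to 0.84 for a true 0.80 in the first illustration). With unequal errors the ratio can move either way, from 0.68 to 1.02. The false share of recorded strokes, about 2% to 18% or 2% to 25% depending on the illustration, rests wholly on assumed inputs. All-cause mortality gains no false events by this route, although its adjustment uses the same baseline covariates.

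The change is worth making because one restriction strengthens the exclusion, the new-user definition, the covariates and the incidence estimate together.

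**What to change.** For the incidence and drug-comparison analyses, but not the prevalence counts:

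- Require at least 12 months of continuous registration before the first AF code and before the first anticoagulant prescription.
- Apply the previous-stroke exclusion and the baseline covariates to all records up to the index date.
- Date stroke outcomes by the date of the event, not the date of entry, and do not count codes for a history of stroke as outcomes.
- Report the results without the registration restriction as a sensitivity analysis.

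The cost is that recently registered patients leave these analyses. The loss falls on AF patients, and in the comparison on anticoagulated ones, so it should be judged against those groups and not against the database of more than 3.5 million. The existing extract must be re-filtered and reanalysed, which needs registration dates to be held in it.

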**Methods:**

The study was conducted in 2 phases. The initial phase was a quantitative analysis of routinely collected primary care data from the Oxford Royal College of General Practitioners Research and Surveillance Center (RCGP RSC) sentinel network database. AF cases from 2009 to 2019 were identified. The study investigated the impact of the use of anticoagulants on complications of AF over this time period. We used this dataset to examine how AF was managed in primary care during the last decade. The second phase involved development of an online dashboard for monitoring management of AF in general practice. We conducted a usability evaluation for the dashboard to identify usability issues and performed enhancements to improve usability.

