## Introduction

Atrial fibrillation (AF) is one of the commonest arrhythmias observed in clinical practice [1]. Globally, the incidence of AF is rising. The thromboembolic complications of AF can lead to significant disabling consequences for patients, including transient ischemic attack, stroke, and pulmonary embolism. Early recognition of AF in general practice can lead to early intervention with managing the risks of these complications.

Current guidelines on the management of AF by the National Institute for Health and Care Excellence (NICE) advise identifying and managing the underlying causes of AF, treating the arrhythmia, and assessing and managing the risk of stroke in these patients [2]. Risk of stroke is determined by the CHA_2_DS_2_-VASc (Congestive heart failure, Hypertension, Age, Diabetes, previous Stroke/transient ischemic attack–VAScular disease) assessment tool [3], which guides the practitioner on commencing anticoagulation treatment to manage this risk. The risk of starting a patient on anticoagulation is assessed using the HAS-BLED (Hypertension, Abnormal renal/liver function, Stroke, Bleeding history or predisposition, Labile international normalized ratio, Elderly, Drugs/alcohol concomitantly) score, assessing for major bleeding risks [4].

Anticoagulation therapy aims to reduce the risk of thromboembolic events. This has been achieved using warfarin (a vitamin K antagonist) for many years. The introduction of direct oral anticoagulants (DOACs) such as apixaban and rivaroxaban to clinical practice has changed how AF is managed in clinical practice [5]. In comparison to warfarin, DOACs are observed to have similar or better mortality and vascular outcomes [6]. They have the added benefit of requiring no monitoring, as opposed to warfarin use [7]. Though studies have highlighted that increased number of patients in clinical practice are receiving treatment for AF [8], whether they are managed according to national or local guidelines is unclear. Better understanding of current management trends of AF in population will guide practitioners on how best to employ interventions in clinical practice to increase awareness of AF and early recognition.

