### Statistical Analysis

Analysis of data extracted from general practice CMR was carried out using the statistical software R. We studied the influence of the anticoagulation regimen by evaluating the cause-specific hazard ratio and the subdistribution hazard ratios of both events. Additionally, we estimated cumulative incidence for both events by direct regression, utilizing the inverse of the probability of censoring weights method [15] with time-varying effects [20]. We will report and interpret both cause-specific and subdistribution analyses. The cause-specific hazard ratio is often interpreted as estimating etiological association, estimating associations between covariates, and the rate at which events occur in those participants who are event-free. The cause‐specific hazard ratio can be interpreted as a rate ratio. Whenever the proportional hazards assumption was violated, we interpreted all hazard ratios as time-averaged effects.

We will determine the (adjusted) incidence and prevalence of AF for each year along with the proportion of incident and prevalent cases treated with nothing, antiplatelet medications only (eg, aspirin), and anticoagulant therapy (warfarin/types of DOACs). We will also determine the number of strokes, transient ischemic attacks, deaths, and bleeds in the incident and prevalent cases per year.

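### The cohort's inclusion rule does not match the stated 2009-2019 newly diagnosed population, and the exposure clock is not tied to registration, so survival needed for inclusion can count as time at risk, mainly on warfarin

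*Protocol article*

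**What the plan says.** Four places in the Protocol article define who is in the DOAC-warfarin comparison, and one sets the clock.

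- Case Ascertainment: adults with an AF code qualify if they were "registered at any point between 2008 and 2019". This limits registration and age. It sets no date for diagnosis or first prescription.
- Study Design: the repeated cross-sectional study was to "identify those patients diagnosed with AF during 2009-2019".
- Abstract, Methods: "AF cases from 2009 to 2019 were identified".
- Introduction, primary objective: whether "people with newly diagnosed AF treated with DOACs versus warfarin have any difference in stroke or all-cause mortality".
- Exposures and Outcomes: "we measured exposure from the first general practice prescription". Exposure is the first continuous anticoagulant prescription after AF diagnosis, and follow-up runs to the end of the study period. No entry date is given, and nothing refers to the patient's registration date.

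The Introduction says of anticoagulation: "This has been achieved using warfarin (a vitamin K antagonist) for many years", with DOACs introduced later. Statistical Analysis plans cause-specific and subdistribution hazard ratios, and cumulative incidence by direct regression, "utilizing the inverse of the probability of censoring weights method".

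**The concern.** A patient is in the database only if alive and registered at some point in the window. Where the first prescription comes before that point, the interval between them is survival required for inclusion (left truncation). Counting it as time at risk adds person-years without deaths and lowers the apparent death rate.

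This can arise in two ways:

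1. **Calendar truncation.** As Case Ascertainment is worded, a patient started on warfarin in 2003 and still registered in 2008 qualifies with a 2003 start. One who started the same day and died in 2006 does not.
2. **Late joining.** A patient diagnosed and started in 2010 who joins a network practice in 2015 meets every stated criterion. One who died in 2013 before joining never appears.

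Both fall more on warfarin, because its starts lie earlier in calendar time. Warfarin mortality is then diluted, and DOACs look worse in the primary comparison even if the drugs do not differ. The cumulative incidence of death on warfarin is understated in the same way. Censoring weights deal with loss at the end of follow-up, not with late entry. A drug-free washout does not help either, because these are true first-time starters.

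**Working it through.** The article gives no event rate, sample size or power for phase 1, so there is no figure of its own to reproduce.

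**Step 1: date logic.**

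| Rule applied | Earliest first prescription | Years before 2008 |
|---|---|---|
| Registration 2008-2019 only | no limit | no limit |
| Diagnosis 2009-2019, prescription after diagnosis | 2009 | 0 |

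With the diagnosis window enforced, calendar truncation is nil. Late joining is untouched, because neither rule ties the prescription to registration.

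**Step 2: size if only the registration rule is applied.** With a constant hazard h in both arms and a true ratio of 1, deaths on warfarin equal h × T_obs, but the naive denominator is T_obs + T_pre. The apparent DOAC:warfarin rate ratio is therefore 1 + T_pre/T_obs.

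Assumed inputs, none from the article: h = 0.05 or 0.08 per year; pre-2008 starts spread evenly over B = 5 or 10 years; in-window starts spread evenly; data end in mid-2019, so L = 11.4 years; a share f of included warfarin patients started before 2008.

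- Mean pre-2008 time among survivors: {[1 − e^(−hB)(1 + hB)]/h²} ÷ {[1 − e^(−hB)]/h}
- Mean observed time, pre-2008 starters: [1 − e^(−hL)]/h
- Mean observed time, in-window starters: {1 − [1 − e^(−hL)]/(hL)}/h

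Results at f = 0.4:

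- h = 0.05, B = 5: the means are 2.40, 8.69 and 4.76 years. T_pre = 0.4 × 2.40 = 0.96. T_obs = 0.4 × 8.69 + 0.6 × 4.76 = 6.33. Ratio = 1 + 0.96/6.33 = **1.15**.
- h = 0.08, B = 10: the means are 4.34, 7.48 and 4.30 years. T_pre = 0.4 × 4.34 = 1.74. T_obs = 0.4 × 7.48 + 0.6 × 4.30 = 5.57. Ratio = 1 + 1.74/5.57 = **1.31**.

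Simulating the same set-up gives 1.04-1.09 at f = 0.1, 1.08-1.17 at f = 0.2 and 1.15-1.31 at f = 0.4. With delayed entry at 2008 it gives 0.99-1.01.

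A Cox simulation lets f follow from calendar time. It assumes mortality of 4-8% per year, a DOAC share of starts rising from zero in mid-2011 to 90% by about 2018, and an end in May 2019. With starts back to 2003 the naive death hazard ratio is 1.27-1.32, and 36-40% of included warfarin patients carry pre-entry time.

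**Step 3: size if the 2009-2019 window is enforced.** With a = T_pre/T_obs in each arm, the apparent ratio is (1 + a_warfarin)/(1 + a_DOAC). It is 1 only if both arms carry the same burden.

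- Late-registration shares fixed equal in both arms (10% or 30%, delay up to 5 years): about 0.99-1.00.
- Shares fixed at 30% on warfarin and 10% on DOAC: about 1.08.
- Joining assigned independently of drug, with the Step 2 calendar pattern: about 1.01-1.03 at 10% joiners, 1.07-1.09 at 30% and 1.15-1.18 at 50%. At 50%, pre-entry time affects 27-30% of warfarin but only 11-12% of DOAC patients.

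The third case shows that joining need not depend on the drug. Earlier warfarin starts are enough to make the burdens unequal. Delayed entry on such data returns 0.95-1.03 across all Cox runs, which is 1 within simulation error.

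**The case against.** The strongest case against is that the article read as a whole already excludes the 2003 starter. The objective concerns newly diagnosed AF, and the Abstract and Study Design give 2009-2019. The broad registration rule may serve the yearly incidence and prevalence tables, which need prevalent cases. Both rules can apply together, one on registration and one on diagnosis. The exposure sentence follows a remark about hospital-started treatment, so it may only say which prescription counts. Handling of entry times is a detail that a condensed article may leave to a fuller document.

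Much of this stands. A reader might infer that pre-2008 warfarin years are definitely in the risk sets, and that the primary hazard ratio is inflated by about 1.3, or by 1.6 to 1.8 if starts reach back to 1998. The article does not support that, because three of its own statements exclude those patients. The simulations also ignore the exclusion for gaps of more than 90 days between prescriptions and the prior-stroke exclusion. The gap rule could remove many long-term warfarin users.

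Two things remain. The only sentence stating inclusion criteria omits the diagnosis window, and no separate rule is given for the DOAC-warfarin cohort. And the diagnosis window does not remove late joiners, who meet every stated criterion. The near-null result for them requires equal late-registration shares in both arms, which is unlikely when warfarin starts are earlier. This is not a complaint about missing detail: the stated inclusion rule and the stated start of exposure do not fit together.

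**Conclusion.** The concern holds in limited form. Case Ascertainment does not match the newly diagnosed 2009-2019 population, and exposure is counted from a prescription that need not fall within registration.

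- If the registration rule alone was programmed, the illustrative death hazard ratio is about 1.3 for starts back to 2003, when the truth is 1.
- If the 2009-2019 window was enforced, calendar truncation is nil. Late joiners leave an illustrative 1.01 to 1.18 for 10-50% joiners. With few joiners, or equal burden in the two arms, the bias is negligible.

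Unequal burden is expected to run against DOACs. All sizes rest on assumed mortality, uptake and joiner rates, a constant hazard, and no modelling of the 90-day gap rule. They refer to death; the effect on stroke was not quantified. The point merits correction because it touches the primary comparison and the remedy is cheap, but it does not show that the reported result is wrong.

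**What to change.** State the rule for the DOAC-warfarin cohort separately from the prevalence analyses, in one of two forms:

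1. Require the first AF code and the first anticoagulant prescription both to fall on or after the 2009 study start and while the patient is registered in a network practice.
2. If other starters are kept, enter them into the risk sets only from the latest of first prescription, study start and registration. Apply this delayed entry in the cause-specific, subdistribution and cumulative-incidence models. In the last two, the weights must allow for late entry as well as censoring, so the first form is simpler.

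The article reports that analysis finished in December 2019. The practical step is therefore to state which rule was programmed, report how many patients in each arm had a first prescription before registration, and rerun the comparison if that number is not trivial.

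The cost is a change to the cohort query or an entry-time argument in the R models. The first form loses patients and the second loses early warfarin person-time, so intervals become slightly wider.
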